### Study objective and research questions

This planned study aims to evaluate the efficacy of a CBT group program (STEpS) developed to provide immediate help before potential individual psychotherapy for patients with somatic diseases and comorbid depressive or adjustment disorders. We expect that self-reported depressive and anxiety symptoms assessed by the Hospital Anxiety and Depression Scale will be reduced to a greater extent in the intervention group compared to the wait-list control group. Furthermore, we hypothesize that the group difference in symptom severity can also be demonstrated two months after treatment, although the effect will be smaller. In addition, we expect that the intervention group will be superior compared to the wait-list control group in terms of self-reported psychological distress, changes in experience and behavior, health-related quality of life, state of self-esteem and subjective need for therapy. We also assume that the acceptance of treatment, assessed by attendance rates and self-reporting, is high. Session questionnaires should provide additional information about the psychotherapeutic process of the newly developed group therapy program.

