The following admission procedure is equivalent for both groups. Patients from both groups receive an appointment for an initial consultation within two weeks after the telephone screening. The initial consultation is conducted by the head of the outpatient clinic. If patients appear suitable for the study at the initial consultation, a research assistant will inform them about the study immediately after the consultation. Patients who are interested in participating will receive materials containing detailed information about the study’s content and procedures, and will be called within one week to schedule an appointment for a Structured Clinical Interview for DSM-IV Axis I Disorders (SCID-I) [39]. At the beginning of the SCID-I interview, we will inform participants about data security and that they may withdraw from the study at any time without any negative consequences (for example, without prolonging the waiting period for individual psychotherapy). Written informed consent will be obtained from all study participants. All SCID-I interviews will be conducted by trained clinicians and will be videotaped for quality assurance if patients give their written consent.

Patients who fulfill all inclusion criteria and none of the exclusion criteria will be randomly assigned to the study conditions. In order to guarantee a continuous group size in the STEpS group program, we decided to use block randomization with a block size of 20 and an allocation ratio of 1:1. The allocation sequence will be created by computer-generated random numbers, and will be carried out by a researcher who is not involved in the enrolment and allocation process. Staff involved in enrollment and allocation do not know the allocation sequence; we will use a sealed envelope system. Study participants will be informed about study exclusion or inclusion, allocation to study condition and further study procedures by telephone.

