### Sample size calculation

The literature indicates moderate effect sizes for group psychotherapy in the target group: in a meta-analysis, an average pre to post effect size of *d* = 0.49 for group psychotherapy for somatic diseases was found [24]. Effect size for group treatment compared to wait-list control (over all patient groups) was also indicated as moderate [24]. Comparable studies examining group psychotherapy for chronically ill patients with comorbid depression using HADS score as the primary outcome indicate moderate to strong effect sizes: Schuster *et al*. [30] found a strong interaction effect (*d* = 0.89) from pretreatment to six months follow-up for their CBT group therapy (six sessions) for patients with coronary or orthopedic diseases and comorbid depression, anxiety or somatoform disorders in comparison to the usual treatment of the rehabilitation clinic. Hambridge *et al*. [29] found a moderate effect from pre to post-treatment (*d* = 0.57) of their CBT group program (six sessions) for patients with coronary artery disease and comorbid depression.

In order to detect a main group effect of *f* = 0.25 [56] when adjusting for baseline severity, we will need a total sample size of 128 participants. This sample size provides a power (1-β) of 0.8 and an alpha of 0.05. Sample size calculations were done with G*power 3 software [57].

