### Statistical analyses

All analyses will be based on the initial treatment assignment (intention-to-treat). Missing data will be treated according to the recommendations of Hair *et al*. [58]. First, the extent of missing data will be determined; then, the level of randomness (missing at random, missing completely at random or missing not at random) will be diagnosed applying Little’s missing completely at random test and t-tests for independent variables. According to Cho and Leonhart [59], data missing completely at random is very unlikely in a rehabilitation research setting, so missing data will probably be imputed with a missing at random-capable method (for example, using multiple imputations).

We plan to use a between-group analyses of covariance (ANCOVA) with baseline scores of the outcome variables as covariates to adjust for baseline differences. With these, we compare differences in the main outcomes between the intervention and control group at post-treatment (T_2_) and follow-up (T_3_) time points. Alpha levels will be adjusted for multiple testing. Cohen’s *d* will be calculated to measure the effect sizes. All statistical analyses will be performed using IBM SPSS Statistics 20. If we fail to achieve the target sample size within the given time frame and resources of our study, we will use analyses of variance (ANOVA) instead. Due to randomization, group differences at baseline (T_1_) will be not likely. We will then test for an interaction effect between group and time from T_1_ to T_2_ and a main effect of group from T_2_ to T_3_.

Explorative analyses will be conducted to examine potential effect moderators (demographic variables and coping style, such as seeking social integration or seeking information). Interaction terms of potential moderator variables and treatment will be created and analyzed by linear regression.

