## Discussion

In this study protocol we describe the study design of a randomized wait-list controlled trial that evaluates the efficacy of a newly developed CBT group program for patients with somatic diseases and comorbid depressive or adjustment disorders, which shall be applied as a first-line treatment prior to individual outpatient therapy. We expect that study participants will benefit from the group program on a clinically significant level when compared with a wait-list control group. Moreover, we will examine the acceptance of the group program and the psychotherapeutic process during group participation.

This trial has some limitations. First, we are not sure if we will achieve the sample size and the power that is needed to calculate ANCOVAs; if not, we will use ANOVAs instead. Second, all outcomes are based on self-reported data. Complementary clinician-rated outcome measures would be beneficial, but cannot be performed due to related effort. With this in mind, we paid particular attention to choosing applied self-report measurements of primary and secondary outcomes that are well validated. Third, the study is designed as a long-term investigation with three measurement points, so missing data are to be considered. Due to the fact that the study participants are motivated to begin a therapy in our outpatient clinic, response rates are expected to be rather high. Nonetheless, missing data will occur and can increase the risk of bias. In order to minimize this risk, we will handle missing data according to the latest recommendations [58, 59].

This study also has several strengths. First, the study has a strong methodology, applying a randomized study design with a wait-list control group and a pretreatment, post-treatment and 18-week follow-up measurement point. The examined intervention was developed based on empirical evidence in a four-stage process and was tested in a pilot group. Applied outcome measurements are widely used and well-validated assessments. Inclusion and exclusion criteria are well proved using SCID-I diagnoses. Even further, inclusion and exclusion criteria are defined as naturalistically as possible, allowing a large spectrum of somatic and mental comorbidities to enhance external validity and keep the study sample comparable to routine patient care.

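### Switching from ANCOVA to ANOVA when recruitment falls short loses precision when the sample is smallest and leaves no test specific to the follow-up visit

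*Protocol article*

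**What the plan says.** The Statistical analyses section plans "between-group analyses of covariance (ANCOVA) with baseline scores of the outcome variables as covariates" and compares the arms at T2 and at T3. It then adds a contingency that applies if the target sample is not reached in the available time: "resources of our study, we will use analyses of variance (ANOVA) instead". Two tests take over: a group-by-time interaction from T1 to T2, and "a main effect of group from T_2_ to T_3". The section supports the change by saying that baseline differences are improbable after randomization.

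The limitations paragraph of the Discussion gives the motive. The authors are unsure of reaching "the sample size and the power that is needed to calculate ANCOVAs; if not, we will use ANOVAs instead".

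The target comes from the Sample size calculation, for a group effect of f = "0.25 [56] when adjusting for baseline severity, we will need a total sample size of 128 participants". That section adds: "This sample size provides a power (1-β) of 0.8 and an alpha of 0.05". Allocation is 1:1.

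The Study objective section states a separate follow-up hypothesis, that "the group difference in symptom severity can also be demonstrated two months after treatment", with a smaller effect expected than at post-treatment.

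**The concern.** The rule treats ANCOVA as the method that needs many patients and ANOVA as the one that manages with fewer. For one baseline covariate in a randomized two-arm trial the reverse holds. Adjustment costs one residual degree of freedom and removes outcome variance, so it is worth most when the sample is small.

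The switch also changes the question. The planned analysis has a contrast at T3. The fallback replaces it with a group main effect over T2 and T3 together, which can be significant because of T2 alone.

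The rule may well be used. According to Trial status, the first participant was enrolled in September 2013 and recruitment was still open in May 2015, and the Discussion lists the possible shortfall as the first limitation. At stake are the power of the primary comparison at T2 and the risk that an effect confined to the end of treatment is reported as sustained.

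**Working it through.** **Inputs.** From the protocol article: f = 0.25 (d = 0.5 for two equal arms), alpha 0.05, power 0.80, N = 128, 1:1 allocation. Not in the article, so assumed: the correlation r between HADS-D scores at different visits (range 0.3 to 0.8), equal SDs across visits, and an illustrative shortfall to N = 100.

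**1. Reproduce the planned sample size.** Noncentral F test, 1 numerator df, noncentrality λ = f²N = 0.0625 × 128 = 8.
- One-covariate ANCOVA, residual df 125: power 0.8014.
- Plain two-group ANOVA, residual df 126: power 0.8015.

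So 128 is the size for a two-group comparison at f = 0.25, and ANCOVA is not what makes it that large. Even with a useless covariate (r = 0) the loss is negligible: 0.5981 to 0.5980 at N = 80, and 0.3379 to 0.3375 at N = 40.

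**2. Precision of the T1-T2 interaction.** With two visits this is a t test on change scores. In units of the outcome variance, the error variance is 2(1−r) for change scores and 1−r² for ANCOVA. The ratio is 2(1−r)/(1−r²) = 2/(1+r), which exceeds 1 for every r below 1. The equivalent share of the sample lost is 1 − (1+r)/2.

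Power at N = 100 on two scales: (a) adjusted effect fixed at f = 0.25, the scale of the sample size statement; (b) raw effect fixed at d = 0.5.

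| r | Variance ratio | Sample lost | (a) ANCOVA | (a) Interaction | (b) ANCOVA | (b) Interaction |
|---|---|---|---|---|---|---|
| 0.3 | 1.54 | 35% | 0.70 | 0.51 | 0.74 | 0.55 |
| 0.5 | 1.33 | 25% | 0.70 | 0.57 | 0.82 | 0.70 |
| 0.7 | 1.18 | 15% | 0.70 | 0.63 | 0.93 | 0.89 |
| 0.8 | 1.11 | 10% | 0.70 | 0.65 | 0.98 | 0.97 |

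For 80% power at raw d = 0.5, ANCOVA needs a total of 118, 98 or 68 patients at r = 0.3, 0.5 or 0.7, and the interaction needs 178, 128 or 78. Read literally, the rule already applies at N = 127, where on scale (a) with r = 0.5 power drops from 0.80 to 0.68.

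**3. What the T2-T3 main effect tests.** It estimates the mean of the two group differences, without baseline. Take a T2 effect of d = 0.5, a T3 effect of zero and a T2-T3 correlation of 0.6:
- mean difference = (0.5 + 0)/2 = 0.25
- variance of the two-visit mean = (1 + 0.6)/2 = 0.8
- standardized difference = 0.25/√0.8 = 0.28
- noncentrality at N = 100 = 0.28 × √(100/4) = 1.40
- probability of significance at two-sided 0.05 = 0.28

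For correlations of 0.5 and 0.7 the probability is 0.30 and 0.27. A test directed at T3 would be significant 5% of the time.

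**4. Baseline differences.** Randomization balances the arms in expectation only. The standard error of the baseline difference is √(4/N) SD. The chance of a gap larger than 0.25 SD is therefore 16% at N = 128, 21% at N = 100 and 26% at N = 80. Chance imbalance becomes more likely in exactly the situation that triggers the rule.

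**The case against.** The strongest reply is that the rule is prespecified, is triggered by recruitment and not by results, and does not inflate the type I error of the hypotheses it actually tests. All of that is true. For T2 the consequence is lost efficiency, not bias.

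Several limits on size also stand:
- The article gives no r, and at a high correlation the T2 loss is small. At r = 0.8 on the raw scale it is about 1 power point at N = 100.
- The interaction subtracts baseline, so chance imbalance adds nothing beyond the 2/(1+r) factor. The imbalance argument applies to the T2-T3 main effect.
- The comparison of 0.8014 with 0.8015 uses a single-visit ANOVA, not the fallback itself. It refutes the stated reason for switching. The loss from the switch is shown separately in step 2.
- T3 data do enter the fallback; what is missing is a test of T3 alone. The unadjusted two-visit mean is not always noisier than a single-visit ANCOVA: its variance is (1+r)/2 against 1−r², which is smaller for r below 0.5.
- The 28% assumes a T3 effect of exactly zero, while the authors expect a smaller, non-zero effect. The section also says that alpha will be adjusted for multiple testing. At illustrative levels of 0.025 and 0.0125 the figure becomes about 19% and 13%.

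These points change the size, not the direction. No value of r below 1 makes the interaction the more precise test of T2, and no adjustment of alpha turns an average over two visits into a test of the second.

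**Conclusion.** The concern holds. The stated reason for the switch is wrong, as the article's own sample size inputs show. The replacement T2 test is less precise than ANCOVA for every r below 1, assuming equal SDs at the two visits. At N = 100 the loss runs from about 18 power points at r = 0.3 to about 1 point (raw scale) or 5 points (adjusted scale) at r = 0.8.

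The second defect does not depend on how large r is. The fallback contains no contrast at T3, so a significant main effect cannot support the hypothesis that the benefit lasts two months after treatment. Under the assumptions in step 3, that test would be significant in 13% to 28% of trials with no T3 effect, depending on the alpha used.

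Because the rule governs the primary outcome and its trigger is a shortfall that the authors themselves anticipate, it must be corrected before analysis.

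**What to change.** Delete the ANOVA contingency in the Statistical analyses section and the matching sentence in the Discussion. State that the baseline-adjusted ANCOVA will be used whatever sample size is reached. One mixed model for T2 and T3 with baseline, group, visit and group-by-visit would serve equally well. Test the follow-up hypothesis by the baseline-adjusted group difference at T3 alone, separately from T2. If recruitment falls short, report the estimate, its confidence interval and the achieved precision.

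The cost is a wording change and no new data. Because the trial is unblinded and already recruiting, the change should be a dated, documented amendment made before outcome data are examined by arm.

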## Discussion

In this study protocol we describe the study design of a randomized wait-list controlled trial that evaluates the efficacy of a newly developed CBT group program for patients with somatic diseases and comorbid depressive or adjustment disorders, which shall be applied as a first-line treatment prior to individual outpatient therapy. We expect that study participants will benefit from the group program on a clinically significant level when compared with a wait-list control group. Moreover, we will examine the acceptance of the group program and the psychotherapeutic process during group participation.

This trial has some limitations. First, we are not sure if we will achieve the sample size and the power that is needed to calculate ANCOVAs; if not, we will use ANOVAs instead. Second, all outcomes are based on self-reported data. Complementary clinician-rated outcome measures would be beneficial, but cannot be performed due to related effort. With this in mind, we paid particular attention to choosing applied self-report measurements of primary and secondary outcomes that are well validated. Third, the study is designed as a long-term investigation with three measurement points, so missing data are to be considered. Due to the fact that the study participants are motivated to begin a therapy in our outpatient clinic, response rates are expected to be rather high. Nonetheless, missing data will occur and can increase the risk of bias. In order to minimize this risk, we will handle missing data according to the latest recommendations [58, 59].

This study also has several strengths. First, the study has a strong methodology, applying a randomized study design with a wait-list control group and a pretreatment, post-treatment and 18-week follow-up measurement point. The examined intervention was developed based on empirical evidence in a four-stage process and was tested in a pilot group. Applied outcome measurements are widely used and well-validated assessments. Inclusion and exclusion criteria are well proved using SCID-I diagnoses. Even further, inclusion and exclusion criteria are defined as naturalistically as possible, allowing a large spectrum of somatic and mental comorbidities to enhance external validity and keep the study sample comparable to routine patient care.

This randomized controlled trial will help to clarify whether the developed CBT group program is an effective treatment to reduce depressive and anxiety symptoms in patients with somatic diseases and comorbid depressive or adjustment disorder. If the group program turns out to be effective, it can be implemented as a first-line treatment option prior to individual outpatient therapy for patients with somatic diseases and comorbid depressive or adjustment disorder. The study results will contribute to better outpatient care of mental disorders in patients with somatic diseases in Germany.

## Trial status

The first study participant was enrolled in September 2013. In May 2015 patient recruitment was not completed.

## Abbreviations

ANCOVA: Analysis of covariance
ANOVA: Analysis of variance
BPSR 2000: Bern Post Session Report 2000
BPSR-G-2000: Bern Post Session Report 2000 modified for groups
BSI: Brief Symptom Inventory
CBT: Cognitive behavioral therapy
CONSORT: Consolidated standards of reporting trials
DALY: Disability-adjusted life years
DSM-IV-TR: Diagnostic and Statistical Manual of Mental Disorders, fourth edition, text revision
DT: NCCN Distress Thermometer
ERIraos: Early Recognition Inventory
GSI: Global Severity Index
HADS-D: Hospital Anxiety and Depression Scale, German version
PHQ-9: Patient Health Questionnaire
SCID-I: Structured Clinical Interview for DSM-IV Axis I Disorders
SF-12: Short Form Health Survey
SSES-revised: State Self-Esteem Scale, revised version
TSK: Trier Scales of Coping with Disease
VEV-VW: Revised short form of Change Questionnaire of Experience and Behavior
